
## Methods

### Study Design

This study is a multicenter uncontrolled intervention trial (iHand). All participants will be assessed 5 times: 3 preassessments, 1 postassessment, and 1 follow-up assessment (Figure 1). SPIRIT (Standard Protocol Items: Recommendations for Interventional Trials) [28] will be used.

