### Participants

We aim to enroll patients with chronic perceived hand function problems, including decreased handgrip strength. Since this impairment is caused by a wide range of disorders, such as acquired brain injury, osteoarthritis, rheumatoid arthritis, spinal cord injury, orthopedic problems or other neurological disorders, we have chosen not to limit the study to a single disorder but rather to focus on the common motor limitation, for which the intervention was developed. Therefore, the study sample is heterogeneous. In each center, a rehabilitation physician or clinical researcher is involved in the identification of potential participants for the study, based on screening of predefined selection criteria. The candidates will be contacted by the professional from that particular center to inform them about the study. When participants are interested, an information letter is sent to them. After 1 week, the health care professional will contact candidates to determine their interest in participating in the study and to answer possible questions. If interested in participating, a physical appointment is scheduled to obtain informed consent form, and then, to complete the screening procedure (some selection criteria require physical tests).

Inclusion criteria are (1) age between 18 and 90 years, (2) being in a chronic and stable phase of disease, (3) having received treatment for limitations in performing activities of daily living due to a decline in hand function (regardless of underlying disorder) at the involved rehabilitation center and department, (4) being capable of at least 10° of active extension of the wrist and fingers and 10° of active flexion of the fingers, (5) having the ability to make a pinch grip between thumb and middle or ring finger, (6) having the ability to put on the glove, (7) having sufficient cognitive status to understand 2-step instructions (judged by personal contact between participant and experienced health care professional), (8) living at home, and (9) providing written informed consent. To ensure that people are able to meet the recommended amount of use, an initial inclusion criterion was that the most affected hand of the participant was the dominant hand; however, due to support of the glove during mainly bimanual activities, this inclusion criterion was removed.

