#### Control Unit

The control unit contains a battery, 3 motors, and a microcontroller. It is worn at the waist, on the hip or on the back of the user, using a clip or belt. A cable connects the control unit with the glove, via a detachable connection located close to the glove. An upper and lower arm strap, both available in different sizes, lead the cable along the arm. Embedded software in the control unit proportionally adjusts the amount of assistive force to help the user close the hand—an increase of force induced by the user and recorded at the fingertips will increase the force applied by the actuators and relaxation of active grip reduces the interaction force recorded by the fingertips, resulting in a gradual decline in force supporting finger flexion. Via a smartphone app, the sensitivity and the amount of force produced by the actuators can be adjusted for each finger by the health care professional, and the configuration—which sensors activate which fingers—can be set (eg, activation of the sensor at the middle finger can be set to actuate both the middle and the ring finger simultaneously). Specific useful combinations of a certain amount of sensitivity, force, and configuration of fingers can be saved as profiles. Profiles can be created for specific activities (eg, carrying heavy objects or grasping small objects such as a paintbrush) or general purposes (eg, a low, medium, or high amount of force, to allow the user to switch during the day). Profiles are individually created by the health care professional in consultation with the user, depending on the individual situation and needs. A maximum of 3 custom-designed profiles can be saved under a specific name at the control unit’s buttons for use by the patient at home.

The control unit can be used for a new participant after the previous participant has completed the intervention. For hygienic reasons, each participant will receive a new glove. Because the glove is not washable, due to the integrated electronics, participants are advised to wear a rubber household glove on top of the Carbonhand glove during activities that may expose the hand to liquids or dirt. The rubber household glove is also provided to the participant.

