### Intervention

Participants wear the Carbonhand glove on their most affected hand. If glove use during the 6-week intervention period is interrupted by unforeseen circumstances (eg, being ill for a few days), the participant is allowed to extend this period to achieve 6 weeks of glove use. The participants are free to choose for which activities, when, and for how long they use the Carbonhand system. However, we will recommend using the system at least 180 minutes per week for 6 weeks during the most common activities of daily living [31], such as lifting and carrying items, performing hobbies, cleaning cooking, and gardening. The recommended intensity of use is based on the findings of a systematic review [32]—a minimum dose of at least 16 hours (which is equal to 960 minutes) is needed to reach a functional effect in the stroke population. During the period of home use, the health care professional has weekly contact by phone to ask about the participants’ experience with the Carbonhand system, to verify adherence to the intervention, to ask if adjustments need to be made to the Carbonhand system’s support profiles, and to respond to any potential problems (eg, device deficiencies, adverse events and serious adverse events) that might arise. Extensive notes are made by the health care professional during these phone calls. When adjustments need to be made to the support profiles on the Carbonhand system during the intervention period, an extra visit (either the participant to the center or the investigator to the participant’s home) will be scheduled. For each participant, all adverse events and serious adverse device effects are reported by the site investigators in the investigators site file and the web-based clinical database during the entire study period. Roessingh Research and Development BV is responsible for informing the Medical Ethical Committee about the occurrence of serious adverse device events.

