### Statistical Analysis

Outcome measures will be analyzed using SPSS statistical software (version 19; IBM Corp). Data from the 3 baseline assessments (T0, T1, and T2) will be averaged (for overall preassessment values). Statistical analysis of the therapeutic effect will be performed on all participants who completed all assessments up to and including T3 and T4. Data from participants who drop out before or during the intervention period will be analyzed separately to analyze the patient characteristics of dropouts, including the reasons for dropout, to identify potentially relevant information regarding reevaluation of target population, device-related issues, to inform proper interpretation of study outcomes.

Normality of data distribution for each outcome measure will be checked by visual inspection and with the Shapiro-Wilks test, prior to analyzing outcome measures. Descriptive statistics will be used for all outcome measures (mean and standard deviation or median and interquartile range as applicable). The overall level of significance will be set to *P*<.05.

In order to assess the effect of the intervention over time, linear mixed models will be used to analyze changes in outcome measures over time. If a significant difference is found between sessions, multiple comparisons are performed with Sidak posthoc analysis. If data are not normally distributed, logarithmic transformation will first be applied to potentially achieve normally distributed data and enable use of linear mixed models for analyses. Otherwise, the Friedman test will be used for nonparametric analysis.

In addition, correlations (Pearson correlation coefficient or the nonparametric Spearman correlation coefficient, depending on data characteristics) between amount of use (measured by diary, Carbonhand system, or Motor Activity Log) or baseline patient characteristics and change in hand function outcome measures will be calculated to evaluate whether an increased dose or specific patient characteristics are associated with better outcomes

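### The dose question is answered only by unadjusted correlations although participants choose their own dose, so baseline hand function could create or hide a dose gradient

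*Protocol article*

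**What the plan says.** The last paragraph of the Statistical Analysis section plans "correlations (Pearson correlation coefficient or the nonparametric Spearman correlation coefficient, depending on data characteristics) between amount of use", with use "measured by diary, Carbonhand system, or Motor Activity Log) or baseline patient characteristics and change in hand function outcome measures will be calculated". The stated purpose is "to evaluate whether an increased dose or specific patient characteristics are associated with better outcomes". The only choice left open is parametric or rank. Use and patient characteristics are each related to change separately; no covariate, partial correlation or regression is named.

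On the dose itself, the Intervention section states: "The participants are free to choose for which activities, when, and for how long they use the Carbonhand system". There is a target, "we will recommend using the system at least 180 minutes per week for 6 weeks", but it is a recommendation and not an assigned level. The amount of support also varies between people: "Profiles are individually created by the health care professional in consultation with the user, depending on the individual situation and needs" (Control Unit). The Participants section explains that several kinds of disorder are enrolled and concludes: "Therefore, the study sample is heterogeneous".

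The Statistical Analysis section averages T0, T1 and T2 into one pre-assessment value, so a baseline for each outcome is already available. The Discussion lists the uncontrolled design, self-report, dropout and cumulative device logging as limitations. It does not mention the self-chosen dose.

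**The concern.** A correlation between use and change describes dose cleanly only if those who used the glove more were otherwise like those who used it less. Here the participant decides, and hand function is an obvious influence on that decision. Weaker hands may need the glove more, or may find it harder to use. Hand function may also determine how much true improvement is possible. A variable acting on both sides can produce a dose gradient when none exists, or cancel one that does.

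The separate correlations between patient characteristics and change do not repair this, because two marginal coefficients do not adjust one for the other. The Baseline Characteristics section lists age, gender, diagnosis, time since diagnosis, affected side and dominant side; baseline strength is not among them.

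What is at stake is how an additional result is read. The trial has no control group, so some readers will give weight to a dose gradient.

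**Working it through.** **Inputs from the article.** Evaluable sample 56 (Sample Size section); significance level .05; unadjusted Pearson or Spearman coefficients; baseline taken as the mean of three assessments. The article states no figure for the dose analysis, so there is nothing of its own to reproduce.

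**Assumed inputs.** The article gives no correlation of baseline (B) with dose (D) or with change (C). Absolute values of 0.2 to 0.5 are assumed. The test is two-sided.

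**1. A gradient created when there is none.** If D and C are independent given B, the expected raw coefficient is r(D,C) = r(B,D) × r(B,C). By Fisher's z, the rejection probability follows from atanh(r) × √(56 − 3) = atanh(r) × 7.28, compared with ±1.96.

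| r(B,D) and r(B,C) | Expected raw r | P<.05, raw |
|---|---|---|
| -0.2, -0.2 | 0.04 | 6% |
| -0.3, -0.3 | 0.09 | 10% |
| -0.4, -0.4 | 0.16 | 22% |
| -0.5, -0.3 | 0.15 | 20% |
| -0.5, -0.5 | 0.25 | 46% |

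Example for -0.4: atanh(0.16) × 7.28 = 1.175; the upper tail beyond 1.96 − 1.175 = 0.785 is 0.216, and the lower tail adds 0.001. Simulation with 20,000 trials per setting gave 10%, 20% and 47% for the -0.3/-0.3, -0.5/-0.3 and -0.5/-0.5 rows. The partial correlation given B rejected in 4.9% to 5.4%, as it must under this model.

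**2. A gradient hidden when there is one.** Take a true partial correlation of 0.35. Then raw r = 0.35 × √[(1 − r(B,D)²)(1 − r(B,C)²)] + r(B,D) × r(B,C).

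- +0.3 and -0.3: 0.35 × 0.91 − 0.09 = 0.23; raw detection 40%.
- +0.5 and -0.3: 0.35 × 0.826 − 0.15 = 0.14; raw detection 17%.
- +0.5 and -0.5: 0.35 × 0.75 − 0.25 = 0.01; raw detection 5%.

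The adjusted analysis detects the effect in 75% to 76% of trials in all three.

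**3. Regression to the mean alone.** Suppose B and C are linked only by measurement error and dose follows true strength. Let single-test reliability be ρ, with total variance 1 and no true differences in change.

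- Var(B) = ρ + (1 − ρ)/3, Var(C) = (1 − ρ) × 4/3, Cov(B,C) = −(1 − ρ)/3.
- At ρ = 0.7: r(B,C) = −0.1 / √(0.8 × 0.4) = −0.18. At ρ = 0.95: −0.0167 / √(0.967 × 0.0667) = −0.07.
- D is unrelated to C, so the raw coefficient is unbiased; simulated rejection was 4.8% to 5.3%.
- Adjustment now introduces bias. At ρ = 0.7 and a dose–true-strength correlation of -0.5, r(B,D) = −0.5 × √(0.7/0.8) = −0.468. The partial correlation is −(0.468 × 0.177) / √[(1 − 0.219)(1 − 0.031)] = −0.095. Then 0.095 × √52 = 0.69, and rejection is about 10.6%.
- For reliabilities of 0.7 to 0.95 and dose–strength correlations of -0.3 and -0.5, simulated adjusted rejection was 5.4% to 10.6%.

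**4. Cost in precision.** At n = 56, the correlation detectable with 80% power is tanh[(1.96 + 0.84)/√53] = 0.367 raw. With one covariate, √52 replaces √53 and it is 0.370.

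**The case against.** The strongest reply is that the article asks only about association, in an analysis added after the main one, and a bivariate coefficient is a legitimate measure of association. That stands. A reader might infer that the trial means to prove efficacy through a dose gradient; the article nowhere says so. The therapeutic effect is assessed by change over time in the mixed models.

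A second reply is that regression to the mean is not the mechanism. A reader might infer that it biases the raw coefficient because change contains the baseline. Step 3 shows that it does not do so alone, and that adjustment then does mild harm. This stands, and it is why the raw coefficient should not be discarded.

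Third, the Participants section describes a range of diagnoses. A reader might infer that it plans a wide spread of severity, but it does not say that, and the eligibility criteria limit severity at the weak end. Severity will still vary, but by an unknown amount.

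Fourth, use is guided by a weekly target, weekly calls that check adherence, and permission to extend an interrupted period. These may narrow the variation in dose, but they do not make it independent of hand function.

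Finally, the magnitudes are assumed. At 0.1 and 0.3 the spurious coefficient is 0.03 and rejection is under 6%; the top figure needs -0.5 on both sides.

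**Conclusion.** The point holds as a limited one. The article fixes an unadjusted method for a dose that participants choose, so this is not a detail left to an unseen analysis plan. If baseline hand function influences both use and true room to improve, the raw coefficient can mislead in either direction. With no dose effect, n = 56 and baseline correlations of -0.2 to -0.5 with both variables, the false-positive rate is about 6% to 47%. With opposite signs and a true partial correlation of 0.35, detection falls from about 75% to between 40% and 5%.

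This is a possibility under assumed values and not a demonstrated bias: the article gives neither the size nor the sign of these correlations. Under the alternative mechanism of pure measurement error, the adjusted analysis is the worse of the two, but its error rate reaches only about 10% under the values assumed. On balance, adjustment is worth adding, beside the raw coefficient and not in its place. The primary grip-strength analysis and the sample sizes of 56 and 63 are unaffected.

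**What to change.** Add to the Statistical Analysis section that, beside each raw Pearson or Spearman coefficient for dose, a regression or partial correlation of T3 change on device-recorded glove use will be reported. It should be adjusted for the participant's averaged T0-T2 value of that outcome and for a broad diagnosis group, for example neurological versus musculoskeletal. Device-recorded use is preferable as the dose because the Motor Activity Log measures use of the affected arm and hand and is itself an outcome at T0-T4.

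Any dose-response statement should rest on both results and be worded as an association, because motivation and early perceived benefit remain unadjusted. If the two results disagree, both should be shown and the disagreement discussed.

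The cost is a sentence or two and no new data. Statistically, it is one degree of freedom for baseline and one for a two-level diagnosis group. There is also the small bias shown above if baseline and change are linked only through measurement error (rejection about 5% to 10% at assumed single-test reliabilities of 0.7 to 0.95). The article reports data collection as ongoing in March 2022, so at that point the addition could still be specified before analysis.

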## Results

The study started in June 2019. The first participant was enrolled on June 25, 2019. As of October 2021, we have enrolled 52 participants. As of March 2022, the study is still ongoing due to the COVID-19 pandemic and related restrictions. We expect data collection to be completed in 2022.

## Discussion

We aim to conduct a high-quality powered clinical trial, to investigate changes in unsupported hand function after 6 weeks of use of a grip-supporting soft robotic glove during activities of daily living by patients with hand weakness and hand function limitations. It is known that several weeks of training using a robotic device improves activities of daily living performance, hand function, and hand strength to a similar extent as conventional training in stroke and other neurological conditions [46]. Yet, robot-assisted training has not been investigated substantially in disorders such as osteoarthritis, rheumatoid arthritis, neuromuscular diseases, even though the training principles share common ground—providing high-dose exercise training to improve hand function. It is conceivable that robot-assisted training could have a positive effect in a wider range of disorders. Nevertheless, exercise therapy might not be enough to halt deterioration over time or to regain hand function to a level required to achieve independence in activities of daily living.

To support activities of daily living that remain very challenging or impossible, assistive technologies can be used. Assist-as-needed principles have been increasingly incorporated in both assistive and therapeutic technology [47]. The Carbonhand system is one such example that allows the performance of functional activities to be enhanced directly while using the affected arm and hand repeatedly during daily activities, to provide high-dose task-specific training. This combination allows a unique approach, extending direct support of activities of daily living with the possibility to stimulate improvement of hand function over time outside of a clinical setting. Findings may allow high doses of training throughout the day into people’s homes, in the most functional task-specific way possible, and possibly prevention of learned nonuse.

To the best of our knowledge, comparison with other studies will be difficult, because this is one of the first user trials that will apply and test a fully wearable robotic system to support hand function at home for unsupervised use during an extended period of multiple weeks. Moreover, other studies [26] that do examine effects of a soft robotic glove focused on examining the direct assistive effect of the glove by comparing performance with and without the glove.

One strength of this powered study is that the sample size calculation was based on results from a previous clinical study [27] that evaluated a similar assistive device. In addition, experiences from the previous study [27]were used in defining the broad range of data collected covering all levels of the International Classification of Functioning, Disability and Health [48], including grip and pinch strength measurements, functional ability measurements of the arm and hand, pain and quality of life questionnaires, semistructured interviews, diaries, and glove-use data. Another strength is the focus on the generalizability of the outcomes for patients with reduced hand strength, by including patients with a wide range of disorders from multiple centers. As a result, we expect that the results of this study will contribute to clinical practice, by identifying the role that assistive devices can play within the rehabilitation process of a wide range of patient groups. In addition, we pay particular attention to protocol adherence and data collection: all professionals involved in the study received extensive training to standardize the execution of the study in the different centers, in the use of the web-based clinical database for data collection, and in fitting and operating the Carbonhand system. Additional plenary instruction sessions for good clinical practice were scheduled. Each of those aspects are explained in detail in instruction manuals, which are available to all involved persons through a website. In addition, visits to each participating center are conducted by an independent monitor to ensure protocol adherence and data integrity. In this paper, we use the SPIRIT-checklist for transparency and completeness in reporting all key elements. Furthermore, dissemination of the study results is planned through presentations at both scientific and clinical conferences and publications in peer-reviewed scientific medical journals, to reach both health care professionals (medical doctors, occupational and physical therapists) and the academic community. The Vancouver Convention is used as guideline to determine authorship and no professional writers will be involved [49]. Upon reasonable request, data will be available from the corresponding author. In addition, press releases will be issued to web-based media and health care magazines with lay summaries of study outcomes to inform potential end users.

In addition to these strengths, we face some challenges. First, the therapeutic effects of Carbonhand will be assessed using an uncontrolled design because of practical reasons—limited availability of resources in terms of project funding and project duration. Second, some outcome measures, for example those assessed with the Motor Activity Log, Michigan Hand Outcomes Questionnaire–Dutch Language Version, Short Form 36, EQ-5D, and the semistructured interview and diaries, are self-reported, which includes the risk of socially desirable answering. Potential bias is reduced as much as possible by allowing participants to complete the questionnaires by themselves, without interference from the health care professional. Finally, participants that might be disappointed about the effect of the glove may have a higher risk of dropout during or directly after the intervention period. This may influence postintervention (T3) and follow-up (T4) results. In order to prevent this effect as much as possible, professionals were instructed to explain the importance of completing the study to all participants at the start of the study. In addition, the characteristics of the dropout sample will be analyzed to inform proper interpretation of study outcomes. Another limitation is the cumulative collection of glove-use data via the Carbonhand system. This means that the exact amount of use per day per week or per bout of activity cannot be retrieved. In order to obtain insight into day-to-day use of the glove, participants are asked to note this information daily in a diary.

This is the first powered clinical trial to investigate the unique application of an assistive grip-supporting soft robotic glove for use outside of clinical settings with the aim to have a therapeutic effect. Despite the abovementioned challenges, the study will provide a solid knowledge base about the therapeutic effect of 6 weeks of home use of an assistive grip-supporting glove.

